## Background

The Joint United Nations Programme on HIV/AIDS (UNAIDS) “90–90-90” goals provide a compelling roadmap toward achieving the end of the HIV epidemic. The UNAIDS plan, which has been embraced by the international public health community and much of sub-Saharan Africa, calls for 90% of those HIV-infected to be aware of their status, 90% of those aware of their status to be on sustained antiretroviral therapy (ART), and 90% of those on ART to be virally suppressed [1]. Achievement of these goals is expected to dramatically reduce or end the HIV epidemic [1, 2]. In parts of sub-Saharan Africa (SSA), early retention in HIV care is a major obstacle to achieving the UNAIDS 90–90-90 goals. While adherence and viral suppression among those remaining in care is high [3], initiation of and retention in ART treatment (the “second 90”) has been challenging. The first year of ART treatment is a particularly vulnerable period: nearly a quarter of people initiating ART are lost to care within the first 12 months, with the majority of loss to care after the first visit or within the first few months of care [4–6].

Comorbid depression renders people living with HIV vulnerable. Comorbid depression affects patients receiving ART [7] as it is a barrier to ART retention [8, 9], associated with reduced ART adherence and viral suppression [7, 10–12].

Malawi, with a population of 17.5 million, has an adult HIV prevalence of 10% [13] and barriers reflecting challenges experienced elsewhere in sub-Saharan Africa. The Malawi Ministry of Health (MoH) has embraced the UNAIDS plans and has been a leader and innovator in expansion of antiretroviral therapy (ART) treatment programs. Yet retention in HIV care has been challenging, with only 76% of adults initiating ART being retained in care at 12 months, and only 65% being both retained in care and virally suppressed [14]. Depression is prevalent among HIV-infected adults in Malawi [15, 16] and is associated with decreased retention in care and viral suppression [7–12, 17–20]. However, Malawi has few psychiatrists and psychiatric wards to provide care [21]. The MoH is working to build capacity through task-sharing approaches, including training primary care providers and outreach workers in mental health screening and counselling [22–24].

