#### Algorithm-based care for depression (ABCD)

We adapted an ABCD antidepressant prescription model. ABCD is a resource-efficient, task-sharing model for delivering high quality, effective, safe antidepressant management in non-psychiatric settings. ABCD equips non-specialists (e.g., primary care clinicians or HIV clinicians) to safely and effectively prescribe and monitor antidepressants. The model trains staff to know what to measure (e.g., depressive severity, side effects, adherence), how and when to measure it, how to interpret the results, and what resulting course of action to pursue (e.g., maintain dose, increase dose, address side effects, switch medication). Key features include (1) treatment decisions guided by regularly measured metrics of depressive severity, side effects, and adherence; (2) an algorithm summarizing best-practices care based on metrics; (3) a treatment goal of remission (full resolution of symptoms); (4) low starting dose followed by dose adjustments until remission, as long as the medication remains tolerable; (5) ensuring an adequate trial (six to eight weeks at moderate to high dose); and (6) regular structured supervision for continuous quality improvement.

In our program, a patient initiates an antidepressant when identified with moderate to severe depressive severity (PHQ-9 score ≥ 10) combined with clinical confirmation of the presence of depression (Fig. 2). Every four weeks at the monthly ART appointment, considered critical decision points (CDPs), the patient reports depressive severity and side effects using standardized measures. These metrics guide a recommendation to increase, maintain, or decrease the antidepressant dose or to change treatments. If the patient is tolerating the medication but depressive symptoms have not remitted, a dose increase is recommended. If side effects are not tolerable, the recommendation is to address them or switch treatment. At CDP3 (i.e., after 12 weeks), the patient has either achieved remission (and enters a maintenance phase) or has demonstrated treatment resistance to the current medication (and receives a new treatment plan).

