### Data analysis

The primary program evaluation question is whether the depression treatment program results in improved HIV and mental health outcomes for patients with HIV and depression relative to the standard of care prior to program implementation. The main analysis will follow an “intent-to-treat” approach, classifying patients according to screening vs. treatment phase (unexposed vs. exposed to the program) without regard to actual treatment received. In our main analysis, we will define our primary outcome, retention in HIV care with viral suppression 6 months after starting ART, as never being more than 30 days late to any scheduled return visit in the first 6 months on ART and having a viral load < 1000 copies/mL at 6 months; patients not retained or not suppressed will be coded as a failure. (Table 2**)** This composite outcome was chosen as the primary outcome because it is the definition of ART clinical success in the Malawian ART treatment system; those not retained and those retained but not suppressed are both clinical failures. This main analysis will estimate the probability of retention and viral suppression 6 months after starting ART using a generalized linear model with binomial error distribution, adjusting for calendar time and potential confounders that are imbalanced between arms at baseline, potentially including age, sex, clinic, PHQ-9 score, and presence of suicidal ideation. We will model these associations using separate generalized linear models among two samples: (a) those with mild, moderate, or severe depression (PHQ-9 ≥ 5) and (b) those with moderate to severe depression (PHQ-9 ≥ 10).

**Table 2 Tab2:** Outcome Variables

	Definition	Type
Primary Outcome		
Retention with Viral Suppression	both attending all ART appointments “on time” through 6 months and having a viral load < 1000 copies/mL at 6 months	Binary
Secondary Outcomes		
Viral Suppression	viral load < 1000 copies/mL at 6 months	Binary
Retention	attending all ART appointments “on time” through 6 months	Binary
	number of ART appointments attended through 6 months	Count
Consistent ART supply	Never going more then 5 days without ART, as calculated from pills dispensed and time between attended appointments	Binary
Depression Remission	PHQ-9 Score < 5 at 6 months	Binary

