In secondary analyses, we will consider ART care retention through 6 months (binary), number of ART appointments attended in the first 6 months (count), maintaining consistent ART supply through 6 months (binary), and viral suppression at 6 months among those retained (binary). Further, secondary analyses will take an “as treated” approach, comparing patients who receive treatment in the treatment phase to all patients during the screening phase; and an “as adequately treated” approach, comparing patients who receive adequate treatment (≥3 consecutive months of protocol-concordant antidepressant prescriptions or ≥ 4 counseling sessions) during the treatment phase to all patients during the screening phase. Data are not available on antidepressant adherence. (Table 3).

**Table 3 Tab3:** Analyses

Analysis	Definition
Primary: “intent-to-treat”	Initiated after program launch
“as treated”	Received depression treatment
“as adequately treated”	≥3 consecutive months of protocol-concordant antidepressant prescriptions or ≥ 4 counselling sessions

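### The secondary 'as adequately treated' contrast has immortal-time bias: exposure is earned inside the 6-month outcome window, but the comparator is every screening-phase patient

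*Protocol article*

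**What the plan says.** The Data analysis section of the Protocol article sets the main analysis as intent-to-treat, "classifying patients according to screening vs. treatment phase (unexposed vs. exposed to the program) without regard to actual treatment received". Its outcome clock starts at ART initiation. Success requires "never being more than 30 days late to any scheduled return visit in the first 6 months on ART" and a viral load below 1000 copies/mL at 6 months.

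Two secondary contrasts define exposure by treatment received:

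- **As treated:** "comparing patients who receive treatment in the treatment phase to all patients during the screening phase". Table 3 defines this as having received depression treatment, with no time limit for starting.
- **As adequately treated:** "≥3 consecutive months of protocol-concordant antidepressant prescriptions or ≥ 4 counseling sessions", against the same full screening-phase group.

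The text gives no landmark, no time-varying exposure and no matching restriction on the comparator. The only limitation stated is that antidepressant adherence data are unavailable. The adjustment set named for the main analysis is calendar time plus baseline characteristics.

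Two other places bear on the point. The section on algorithm-based care puts antidepressant review at the monthly ART visits, the same visits that define retention. The Background describes loss in the first year of ART "with the majority of loss to care after the first visit or within the first few months of care".

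**The concern.** To be adequately treated by the antidepressant route, a patient needs "consecutive months of protocol-concordant antidepressant prescriptions", three months at least, and so must have kept attending for part of the window in which attendance is the outcome. The counselling route likewise needs four sessions after entry. A treatment-phase patient who leaves after the first visit cannot qualify and drops out of the contrast. The same kind of patient in the screening phase stays in and counts as a failure. Baseline covariates cannot correct a selection made on attendance after baseline.

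The risk lies in interpretation. If the estimates rise from intent-to-treat to as treated to as adequately treated, the pattern will look like dose-response, although part or all of it could come from the definitions. The design is not randomised, and the Discussion says the findings will feed directly into national mental-health planning. Readers may lean on these contrasts, most of all if the intent-to-treat result is null.

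**Working it through.** **1. The plan's own figure.** Population and sample size states 80% power for 60% vs 72% with n = 502. Assuming two-sided alpha 0.05, a two-proportion calculation gives 81.2% at 1:1 allocation and 80.9% at 1:1.25. For n = 131 and 60% vs 82% it gives 79.9%. The stated power is reproduced, so 60% and the 12-point difference are fair reference values. The article gives no figure for the treatment-received contrasts.

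**2. Bias under no effect.** Let p = 0.60 be success in both phases, and q the share who fail on retention before they can qualify. Suppose none of these early failures can qualify and that qualifying is otherwise unrelated to outcome. Then

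- exposed group: p/(1−q)
- all screening-phase patients: p
- spurious difference: p/(1−q) − p

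| q (assumed) | Exposed | Comparator | Spurious difference |
|---|---|---|---|
| 5% | 0.60/0.95 = 63.2% | 60% | +3.2 points |
| 10% | 0.60/0.90 = 66.7% | 60% | +6.7 points |
| 15% | 0.60/0.85 = 70.6% | 60% | +10.6 points |
| 20% | 0.60/0.80 = 75.0% | 60% | +15.0 points |

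The full 12-point design difference appears when 0.60/(1−q) = 0.72, that is q = 1 − 0.60/0.72 = 16.7%.

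**3. What the documents say about q.** Only indirect information: in the Background, nearly a quarter of people starting ART are lost within 12 months, most of them early. No 3-month figure is given, so every q above is an assumption.

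**4. Simulation of monthly visits with no programme effect.** Assumptions: 6-month retention 70 to 80%, composite success 60 to 65%, and 30 to 50% of losses after the first visit.

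- As adequately treated (three monthly visits needed): composite inflated by about 7 to 20 points, retention by about 10 to 23 points.
- As treated: about 0 if every treated patient starts at the ART-initiation visit, about 2 to 5 points if half start later, and about 5 to 12 points if all start later.

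**5. False positives.** With an assumed 244 screening-phase and 100 adequately treated patients and no true effect, the chance of a significant result in favour of the programme is about 45% at q = 15% and 77% at q = 20%, against a nominal 2.5% in that direction.

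**6. Effect of a common landmark.** If both phases keep only patients still in care and on time at the landmark, the comparator also becomes p/(1−q). At q = 15% both groups stand at 0.60/0.85 = 70.6%, and the difference is 0.

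**The case against.** Much of the case on the other side stands, and it limits the point.

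- **Status.** Both contrasts are secondary, and Table 3 marks only intent-to-treat as primary. A reader might infer that the trial's main result is compromised. It is not: classification by phase has no exposure to accrue, so the primary hypothesis and the power statement are untouched.
- **'As treated'.** A reader might infer that this contrast is equally biased. The documents do not support that. Screening takes place at ART initiation, and "a patient initiates an antidepressant when identified with moderate to severe depressive severity (PHQ-9 score ≥ 10) combined with clinical confirmation", so treatment can start at the first visit with no survival needed to qualify. The share of later starters is not given. What remains is ordinary selection by uptake. Its direction is uncertain, because uptake may also follow severity.
- **Size.** A reader might take 8 to 15 points as the expected bias. The formula is an upper-range case. Failure means one visit more than 30 days late, and such a patient can return and still qualify, since no deadline is set. Three monthly prescriptions begun at initiation can be complete at the month-2 visit. Of the 502 patients, 502 − 131 = 371 (74%) score 5 to 9 and are assigned counselling, for which no session spacing is stated. Faster sessions would need less time in care.
- **Other outcomes.** For suppression among those retained, both groups are already limited to retained patients, so the mechanism largely disappears. For depression remission the direction is unclear, because persistent symptoms can prolong treatment.

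None of this removes the core defect. A patient lost after the first visit cannot be adequately treated by either route, and the comparator keeps such patients. Nor can it be left to an unseen analysis plan, since the article itself fixes both the exposure and the comparator.

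**Conclusion.** The 'as adequately treated' contrast is wrong as written for retention, visit count, ART supply and the primary composite. The bias comes from the definitions and favours the programme. Under no effect and 60% success it is at most about 3 points at q = 5% and 15 points at q = 20%, and would match the 12-point target at q = 16.7%. These figures rest on an assumed q, and the bias is smaller to the extent that patients who fail can still qualify. The 'as treated' contrast is affected only in so far as treatment begins after the ART-initiation visit. This should be corrected before the secondary analyses are run, but it does not threaten the primary analysis.

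**What to change.** 1. Do not compare the adequately treated with unrestricted screening-phase patients. Set one landmark for both phases, for example still in care and on time at month 3. Classify exposure by what has accrued by then, count outcomes only after it, and adjust or weight on baseline covariates. Modelling treatment as time-varying is an acceptable alternative.
2. For 'as treated', count only treatment started at the ART-initiation visit, or use the same landmark.
3. Label both contrasts exploratory and subject to residual selection by uptake, and state that a rising sequence of estimates is not evidence of dose-response.
4. Optionally add an estimate with phase as the instrument, as a sensitivity analysis with its assumptions stated. It assumes no secular trend in outcome beyond what is adjusted for. It also needs an exclusion restriction, which fails for adequate treatment if partial treatment has any effect. Phase is also not randomised, so this estimate should not replace the contrasts.

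The cost is revised wording, some extra programming on visit dates already being abstracted, and wider intervals. Landmark estimates do not capture effects on early loss, when most loss occurs. The intent-to-treat analysis does capture them and should carry that question.

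### The secondary 'as adequately treated' contrast removes early losses from the treated group but keeps them as failures in the comparator, which pushes retention-type outcomes towards apparent benefit

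*Protocol article*

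**What the plan says.** The Data analysis section describes the contrast as "comparing patients who receive adequate treatment (≥3 consecutive months of protocol-concordant antidepressant prescriptions or ≥ 4 counseling sessions) during the treatment phase" set against all patients of the screening phase. Table 3 repeats the exposure rule: "≥3 consecutive months of protocol-concordant antidepressant prescriptions", or at least four counselling sessions. Neither place puts any attendance or time-in-care condition on the screening-phase group.

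Three other statements determine what this does:

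- **Where antidepressant treatment is reviewed.** The ABCD section places it "Every four weeks at the monthly ART appointment, considered critical decision points (CDPs". Under Measures, new patients generally receive 30 days of ART and a return date 30 days ahead, and these same visits define retention.
- **How loss is scored.** The primary outcome requires "never being more than 30 days late to any scheduled return visit in the first 6 months on ART" together with viral suppression, and "patients not retained or not suppressed will be coded as a failure".
- **When loss occurs.** The Background says that nearly a quarter of those starting ART are lost within 12 months, "with the majority of loss to care after the first visit or within the first few months of care".

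The main analysis is different. It classifies patients by phase, whatever treatment they received.

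**The concern.** Exposure is not known at ART start. It builds up over return visits that fall inside the outcome window. A treatment-phase patient who never comes back after the first visit cannot accumulate three months of prescriptions and so is not in the exposed group. The identical screening-phase patient remains in the comparator and is scored as a failure. No difference in patient type or in willingness to accept treatment is needed for the two groups to diverge.

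The adjustment variables named for the main model (calendar time, age, sex, clinic, PHQ-9 score, suicidal ideation) are all fixed at ART start. Adjusting for them cannot remove a condition that is met afterwards.

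What is at stake is interpretation. A null phase-based result beside a favourable adequately-treated result invites the reading that the programme works when delivered in full. The Discussion says the findings will feed into national mental health planning, and the article attaches no caution to this contrast.

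**Working it through.** **1. The plan's own figures.** With a two-sided 5% test and 1:1 allocation (both assumed, as neither is stated), 502 patients give 81.2% power for 60% v 72%, and 131 patients give 79.9% power for 60% v 82%. Both agree with the stated 80%. The detectable differences of 12 and 22 points therefore stand as benchmarks for the full phase comparison.

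**2. Inputs.**
- Composite success of 60%: the base rate in the article's power example.
- Six-month retention R: not given. The Background gives 76% at 12 months. I use 76–80%, with 70–85% as a wider range.
- Share f of six-month loss that falls before the third prescription: not given. The Background says the majority of loss is early. I use 50–75%.
- True treatment effect: zero.
- Patients who fail early do not return and qualify, and among those still in care, adequate treatment is unrelated to outcome.

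**3. Antidepressant route.** The share still in care when the exposure is completed is S = 1 − f(1 − R). Every success is in this share, so the exposed group's success rate is 0.60/S, against 0.60 in the comparator.
- R = 0.80, f = 0.50: S = 1 − 0.50 × 0.20 = 0.90. Composite 0.60/0.90 = 66.7%, **+6.7 points** (ratio 1.11). Retention 0.80/0.90 = 88.9%, +8.9 points.
- R = 0.76, f = 0.75: S = 1 − 0.75 × 0.24 = 0.82. Composite 0.60/0.82 = 73.2%, **+13.2 points** (ratio 1.22). Retention 0.76/0.82 = 92.7%, +16.7 points.

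**4. Wider range for the composite, f from 50% to 80%.**

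| R | Spurious gain (points) |
|---|---|
| 0.85 | +4.9 to +8.2 |
| 0.76 | +8.2 to +14.3 |
| 0.70 | +10.6 to +18.9 |

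**5. Loss spread evenly.** If each of six visits is kept with probability c = R^(1/6) and k returns are needed, the gain is 0.60/c^k − 0.60. At R = 0.76, c = 0.955.
- k = 2: +5.7 points.
- k = 3: +8.8 points.

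**6. Counselling route.** Patients with PHQ-9 of 5–9 are assigned counselling: (502 − 131)/502 = 371/502 = 74% of the sample. The article does not say how sessions are spaced. If four sessions need only one return visit and loss is even, k = 1 gives +1.6 points (R = 0.85), +2.8 (R = 0.76) or +3.7 (R = 0.70). The gain would be larger if loss clusters after the first visit.

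**7. Same condition in both phases.** If screening-phase patients must also be in care at the same point, their success rate is 0.60/S as well, and the expected difference under no effect is zero.

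**The case against.** Several points on the other side stand and limit the claim.

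- **It is a secondary contrast.** The primary analysis compares phases and is untouched.
- **Months in care are not shown to be necessary for everyone.** A reader might infer that only patients who stay for months can qualify. The article supports this for antidepressants. Counselling is delivered by community health workers with separate records, and nothing ties the four sessions to monthly ART visits.
- **The exposure does not contain the whole outcome.** A patient can qualify by month 3 and fail in months 4–6. Failure also means being over 30 days late once, so a patient can fail early, return and still qualify. The formula in step 3 assumes that nobody does.
- **A benefit is not guaranteed.** It is tempting to say the contrast would show benefit even if treatment did nothing. That is only the expected direction of this mechanism. Other selection, such as longer treatment of patients whose symptoms persist, could pull the other way.
- **The size is not established as equal to the study's target effect.** Only the top of the 7–13 range reaches 12 points. That benchmark belongs to all 502 patients, most of them assigned counselling. In the PHQ-9 ≥ 10 sample, where antidepressants are first-line, the benchmark is 22 points. The timing of loss is also borrowed from 12-month loss to care, a different event from six-month lateness.
- **Some detail may sit in an analysis plan not shown.** The missing time window for treatment is not a separate defect, and the article does not say which outcomes this contrast will use.

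The comparator is not such a detail. The article fixes it as unrestricted, with adequate treatment counted "during the treatment phase to all patients during the screening phase", so an analysis plan would have to depart from the published text to repair it.

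**Conclusion.** The asymmetry is real and should be fixed. Exposure requires returning after ART start, the comparator has no matching requirement, and non-retention is scored as failure. For any retention-type outcome used in this contrast (retention, the composite, visit counts, ART supply), the mechanism favours the treated group.

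Its size rests on assumptions. For the antidepressant route the spurious composite gain is about 7 to 13 points, given zero effect, 60% success, 76–80% six-month retention, 50–75% of losses before the third prescription and no return after failure. For counselling it could be as low as about 2 to 4 points, if one return suffices and loss is even. The pooled figure depends on the mix of routes among qualifying patients, which the article does not give. Other selection could partly offset it. The phase-based primary analysis is not affected.

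**What to change.** Do not compare adequately treated patients with all screening-phase patients on retention-type outcomes. Any one of these would do:

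1. **Landmark with one condition for both phases.** Include only patients who, by the landmark, have actually attended the ART visits needed to complete the exposure and have not already failed. Classify treatment only up to the landmark, ignore later treatment, and count outcomes only after it. State the counselling session spacing so that the landmark suits both routes.
2. **Clone-censor-weighting** from ART start.
3. **Drop retention-type outcomes** from this contrast.

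For option 1, requiring no visit more than 30 days late by day 90 is not enough. A patient last seen at day 30 has a day-60 visit that is exactly 30 days late at day 90, so still meets the rule and then fails. An antidepressant patient with prescriptions at days 0, 30 and 60 must have attended day 60. The condition has to be attendance itself.

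Report losses before the landmark by phase, so that any early programme effect remains visible.

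The cost is a paragraph of analysis text and modest programming on records already being abstracted. The downside is fewer patients and an estimate that applies only to those in care at the landmark. Selection by who takes up treatment would remain and should be acknowledged.
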